##### Intervention Usage

Intervention usage was objectively tracked using Google Analytics (Google LLC) and through the Qualtrics Survey Platform (Qualtrics). This included device used, website visit duration, number of pages viewed, and links accessed, including whether participants accessed the quiz, goal setting, and creating strategies components. For the goal setting and creating strategies components, the number of goals and strategies set was also recorded.

##### Recruitment and Retention

The number of individuals enquiring, screened for eligibility, consenting, randomized, completing the intervention, completing process evaluation, and completing follow-up were recorded.

#### Impact Evaluation Measures

##### Diet Quality

Dietary intake was assessed using the validated Australian Eating Survey Food Frequency Questionnaire (AES FFQ) [51], a self-administered 120-item semi quantitative FFQ, with participants being asked to report usual intake over the previous 3 months. Diet quality—Australian Recommended Food Score (ARFS)—was derived from FFQ responses. ARFS is calculated using a subset of 70 items from the AES FFQ relating to intake of fruits, vegetables, meat and flesh foods, nonmeat and flesh protein foods, breads and cereals, dairy foods, and water and spreads and sauces [52]. The ARFS is a summation of points scored for each item, with most items scoring 1 point for a consumption frequency of greater than or equal to once per week, and the total score ranging from 0 to 73 points. A higher ARFS reflects higher diet quality, including greater variety, more optimal nutrient intakes, and closer alignment with the Australian Dietary Guidelines [44].

##### Dietary Intake Related to the Target Eating Behaviors

Intake of fruits, vegetables, discretionary foods, and breakfast were determined from the AES FFQ. This included grams per day and the ARFS subscale for fruits and vegetables, percentage of daily energy intake for discretionary foods, and days per week for breakfast *(Never, 1-2 days, 3-4 days, 5 or more days).*

##### Alcohol Intake

Alcohol intake was assessed using 2 items from the New South Wales Adult Population Health Survey [35], including frequency of alcohol consumption and number of standard drinks usually consumed per drinking occasion.

##### Self-Efficacy for Performing Target Eating Behaviors

Self-efficacy for performing the target eating behaviors was assessed using questions derived from the Project EAT II Survey for Young Adults [53]. The participants were asked to rate their level of confidence on a scale of Not at all confident (1) to Very confident (4) for each behavior, for example, Eat at least 2 serves of fruit each day.

##### Quality of Life

Quality of life was assessed using the Quality of Life Enjoyment and Satisfaction Questionnaire short form [54]. The participants were asked to rate their satisfaction over the previous week on a scale of very good (5) to very poor (1) for each of the 14 items, for example, physical health.

##### Well-Being

Well-being was assessed using the World Health Organization-Five Well-being Index [55]. The participants were asked to rate how they were feeling over the previous 2 weeks on a scale of all of the time (5) to at no time (0) for each of the 5 statements, for example, I have felt cheerful and in good spirits.

#### Measures of Potential Contamination

Included in the follow-up survey were 3 items that assessed what, if anything, the participants had used to help them change their eating behavior as a means of assessing potential contamination of intervention effects. These included whether participants had made changes to their eating behavior over the previous 3 months *(Yes or No)*, and, if yes, an open-response item asking participants to describe the changes; and included a multiple-choice question asking participants to indicate what they had used to help them change behavior, for example, EATS, other research study, program—for example, Lite n’ Easy or Weight Watchers—and other.

### Data Analysis Plan

Data will be analyzed using Stata software version 14.1 (StataCorp LLC). Process evaluation data will be reported as means and SDs for quantitative questions, for example, scoring of individual program components such as usefulness of the goal-setting feature, and open question responses, such as suggested improvements for EATS, will be compiled and described qualitatively. Intervention usage will be assessed via analysis of usage metrics, including the time spent completing individual components and number of times the links were accessed, to allow comparison with other electronic health (eHealth) research studies. Impact evaluation, that is, to determine the efficacy of the EATS program compared with the control, will be determined using an intention-to-treat approach. All the results for all the participants who enter the study will be included in the analyses. Analyses will assess the difference between the intervention and control groups for the change from baseline to 3 months for all outcomes. Each study effect will be tested as the group by time interaction using a linear mixed model where time will be treated as a repeated measure. The effect sizes and 95% CIs will be reported for each outcome measure. A sensitivity analysis will be conducted to explore the impact of missing data on the primary impact evaluation measure (diet quality).

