#### Phases 5 to 7: Implementation, Process, and Impact Evaluation

Phase 5, implementation, involves finalizing the implementation and evaluation plans and support of program delivery before implementing the program. Phase 6, process evaluation, assesses program acceptability and usage, as well as recruitment and retention (primary outcomes). Phase 7, impact evaluation, assesses change in behavior or determinants of behavior [22]. Diet quality is a primary outcome, whereas all others are secondary outcomes. The plans for process and impact evaluation are outlined below.

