### Study Design

The EATS intervention was evaluated in a pilot randomized controlled trial (RCT) with participants randomly allocated to the EATS intervention or attention control group from February to March 2018 and followed up from May to July 2018. Measures were collected at baseline and 3 months after baseline, with the exception of program acceptability (measured post intervention completion) and intervention usage (measured in real time). A diagram of the study timeline and flow is presented in Figure 4. Ethics approval was obtained from the UON Human Research Ethics Committee (H-2017-0404), and the trial was registered with the Australian New Zealand Clinical Trials Registry (ACTRN12618000118202p).

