#### Sample Size

As this is a pilot study, a formal sample size calculation was not performed. The total sample size was set at 126 (ie, 63 per group). This would exceed the median sample size of 30.5 among nondrug trials in a review of the methods and conduct of pilot and feasibility trials [49], ideally allowing for more diversity within the sample in terms of sociodemographics and student-related characteristics, and this was also based on the time available for recruitment to allow the study to be conducted within the university semester (5 weeks), as well as study funding. As males are often underrepresented in health behavior research, a lower limit of 30% of the target sample size being male was set, which would exceed the proportion of males typically achieved in previous intervention studies among this target group [7]. To maximize the number of male participants enrolled, interested females were waitlisted once the proportion of females reached 70% of the target sample size. As the proportion of 30% male participants was unable to be reached, female participants were invited from the waitlist until the recruitment period was complete.

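### The group-by-time mixed model states no baseline adjustment; if the group main effect is left free, it is valid but less precise than a common-baseline model, by (1 − rho)/2 in variance

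*Protocol article*

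**What the plan says.** The Data Analysis Plan section of the protocol article sets the target of estimation: "Analyses will assess the difference between the intervention and control groups for the change from baseline to 3 months for all outcomes". It then gives the method: "Each study effect will be tested as the group by time interaction using a linear mixed model", with time as the repeated factor. The approach is intention-to-treat, and the section says that every participant who enters the study is included. It also promises: "The effect sizes and 95% CIs will be reported for each outcome measure".

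For the impact measures there are two time points. The Study Design section says: "Measures were collected at baseline and 3 months after baseline". Among these measures diet quality has priority. The section on Phases 5 to 7 says: "Diet quality is a primary outcome, whereas all others are secondary outcomes".

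The Sample Size section sets 63 participants per group and states: "As this is a pilot study, a formal sample size calculation was not performed".

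The article does not list the fixed effects of the model. It mentions neither baseline as a covariate nor a constraint that the groups share a baseline mean.

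**The concern.** The ordinary reading of a group-by-time mixed model is group, time and their interaction, all freely estimated. With two time points, that model estimates a separate baseline mean for each group and subtracts the whole observed baseline difference from the follow-up difference. In a randomized trial the expected baseline difference is zero, so an observed difference is chance. Subtracting all of it over-corrects whenever rho is below 1.

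The stake is precision. The intervals for diet quality, and for the other continuous outcomes analysed this way, would be wider than the same data can support. The number of participants was fixed by recruitment time and funding, and follow-up has ended, so the analysis is the remaining place to gain precision. The baseline values it needs are already collected.

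**Working it through.** **The plan's own figure.** The only number to reproduce is the total: 2 × 63 = 126, as stated. The article gives no power, detectable difference, SD, correlation or dropout figure.

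**Inputs.** From the article: two time points, n = 63 per group, 95% intervals. Assumed: rho from 0.3 to 0.9, equal SDs at both times, and either complete follow-up or a share d = 20% missing at 3 months.

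**Step 1, complete data.** In units of 2σ²/n:

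- Group-by-time interaction with a free group main effect: variance 2(1 − rho).
- Baseline-adjusted estimate: variance 1 − rho² = (1 − rho)(1 + rho).
- Ratio of adjusted to planned: (1 + rho)/2. Precision lost: 1 − (1 + rho)/2 = (1 − rho)/2.
- Narrowing of the confidence interval after adjustment: 1 − √((1 + rho)/2).

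**Step 2, a share d missing at 3 months.**

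- Free group main effect: (1 − rho²)/(1 − d) + (1 − rho)².
- Common baseline mean: (1 − rho²)/(1 − d).
- At rho 0.5 and d = 0.2: 0.75/0.8 = 0.9375; 0.9375 + 0.25 = 1.1875; loss 0.25/1.1875 = 21%.
- At rho 0.8 and d = 0.2: 0.36/0.8 = 0.45; 0.45 + 0.04 = 0.49; loss 0.04/0.49 = 8%.

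| rho (assumed) | 2(1 − rho) | 1 − rho² | Ratio | Loss, complete data | CI narrowing, complete data | Loss, 20% missing |
|---|---|---|---|---|---|---|
| 0.3 | 1.40 | 0.91 | 0.65 | 35% | 19% | 30% |
| 0.5 | 1.00 | 0.75 | 0.75 | 25% | 13% | 21% |
| 0.8 | 0.40 | 0.36 | 0.90 | 10% | 5% | 8% |
| 0.9 | 0.20 | 0.19 | 0.95 | 5% | 2.5% | 4% |

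**Step 3, check by simulation at 63 per group, complete data.** Over 20,000 runs, comparing the difference in mean change with a baseline-adjusted regression, the loss was 24.6% at rho 0.5 and 8.8% at rho 0.8, against 25% and 10% by formula. In one simulated data set (rho 0.65), the interaction from the mixed model and the difference in mean change were both 0.1467. The standard error was 0.160 for the interaction and 0.144 for the common-baseline mixed model.

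**Step 4, effect of a chance imbalance.** The baseline difference between groups has standard deviation √(2/63) = 0.18 SD. Given an observed imbalance b, the change estimate shifts by about (1 − rho) × b in the opposite direction. For b = 0.18 SD the shift is about 0.09 SD at rho 0.5 and 0.04 SD at rho 0.8. The planned standard error already allows for this variation.

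**The case against.** The strongest reply is that the article is silent rather than wrong. It never says that the group main effect is free. A model with time and a group-by-3-month term is itself a group-by-time mixed model, and exact model terms are often left to a fuller document. This stands in part: the loss is conditional on the ordinary reading, and if the team already constrains the baseline means there is none. But the article does fix the target as a difference in change and the test as the interaction, and nothing in it points to the constrained form.

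A second reply is that the planned analysis contains no error. That stands. A reader might infer that the test is invalid, or biased by baseline imbalance. The documents do not support this: under randomization the estimate is unbiased and its standard error covers chance imbalance. The cost is efficiency only.

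Third, a reader might attach one figure to the loss, or say that the trial falls short of its power. The article supports neither. It gives no correlation, so any percentage rests on an assumption, and it makes no power claim that could be undermined. The variance scale also looks larger than the effect on the intervals, which narrow by 13% at rho 0.5 and 5% at rho 0.8.

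Finally, equality with the difference in mean change is exact only with complete data. With dropout, the mixed model also uses participants who have a baseline value alone.

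**Conclusion.** The point holds as a recoverable loss of efficiency, not as a fault of validity. If the group main effect is freely estimated, the planned interaction loses (1 − rho)/2 of the precision available with complete data: 35% to 5% over rho 0.3 to 0.9, with intervals about 19% to 2.5% wider than needed when measured against the planned width. With 20% missing follow-up the loss is 30% to 4% over the same range. The result assumes equal SDs at the two times and an unknown rho, and the dropout rate is also an assumption. The improvement is worth making because it uses data already in hand and diet quality is a primary outcome. The pilot purpose keeps the consequence modest.

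**What to change.** State the fixed effects, and fit the same linear mixed model with the group means constrained equal at baseline: a time term and a group-by-3-month term, no group main effect, and an unstructured 2 × 2 covariance for the two measurements. Participants with a baseline value only stay in, as the Data Analysis Plan section requires.

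Complete-case ANCOVA on the 3-month value should not be offered as an equivalent. It drops participants without follow-up, whom the plan says will be included.

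The cost is about one line of model code and no new data. The constraint relies on baseline having been measured before allocation was known, which should be confirmed. The Results section says that data collection is complete and analysis is under way. The change should therefore be documented before any group comparison is seen. If that is no longer possible, report it as a dated change, with the model as published shown alongside.

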## Results

The pilot RCT has now been completed; the collection of the 3-month follow-up data was completed on July 12, 2018. Data analysis is currently being conducted.

## Discussion

### Principal Findings

This project used the PRECEDE-PROCEED model to develop a brief Web-based nutrition intervention for young adult university students and plan the evaluation. Nutrition interventions are needed in this target group because of the high rates of unhealthy eating behaviors and the known impacts of this on health and well-being and long-term chronic disease risk [56]. The difficulty is in engaging young adults because of the transitional nature of this life stage and the many factors influencing their health behaviors [9].

The pilot RCT will evaluate whether EATS is deemed acceptable and appropriate by young adult university students and whether it can improve diet quality over a 3-month follow-up period. The process evaluation will provide important feedback from the target population on the appropriateness of the mode of delivery, intervention duration, and individual intervention components. This will be utilized to update and modify the intervention, whereas the intervention usage data will be compared with other eHealth studies to assess participant engagement. Utilizing the university setting, as well as the eHealth mode of intervention delivery, shows promise as a means of effectively targeting and engaging young adults [14,57]. In addition, the development of EATS as a brief intervention draws on the precedence of successful brief interventions to reduce alcohol use among university students [20]. Therefore, the combination of a strong methodological approach to intervention development, the use of a setting with the potential for wide reach among young adults, and the use of an intervention approach with demonstrated efficacy suggest that the EATS intervention may be successful.

### Implications

If the evaluation results are positive, the potential implications will be significant in terms of translation and addressing the important health problem of poor diet among young adult university students. The long-term goal of this project is translation into University Health Promotion, that is, to implement EATS as a readily available program for all UON students, facilitated by the University Health Promotion staff. The key strategy to achieve this is the engagement of the steering committee, including key stakeholders to assist in translation. Furthermore, the chosen mode of delivery (ie, automated website) minimizes the ongoing resources required for program delivery. This paper adds to this evidence base and provides a detailed example for future researchers and health professionals working with this group and setting. If successful, there is also the potential that the intervention could be transferable to other universities nationally or internationally.

## Abbreviations

AES FFQ: Australian Eating Survey Food Frequency Questionnaire
ARFS: Australian Recommended Food Score
BCT: behavior change technique
EATS: Eating Advice To Students
eHealth: electronic health
RCT: randomized controlled trial
SCT: social cognitive theory
SHLS: Student Healthy Lifestyle Survey
TPB: theory of planned behavior
UON: University of Newcastle
